### Hypotheses and research questions

The two hierarchically ordered primary hypotheses are: In MAFT-D compared with TAU, a stronger reduction of patient-rated depressive symptoms (first primary endpoint) and a lower rate of patient dropout (second primary endpoint) is expected from baseline to 20 weeks after baseline. The study’s hierarchical testing framework first assesses symptom reduction, followed by dropout rates. While this sequence reasonably suggests that dropout rate effects might be less relevant without significant symptom reduction, we would like to point out that one could also argue that both hypotheses hold independent value and could merit separate evaluation, given their relevance to treatment quality. While the time point (after 20 weeks) was chosen carefully to ensure comparability with other studies, it carries the risk that the intervention dose might be insufficient at this stage, with effects potentially becoming evident only at later follow-ups.

Secondary patient-related hypotheses are: In MAFT-D compared with TAU, stronger reduction of patient-rated depressive symptoms after 35 weeks, and 20 and 36 months, lower rate of dropout at week 35 and month 20 and 36, stronger reduction of observer-rated depressive symptoms, and patient-rated anxiety, somatic complaints, personality structure deficits, interpersonal problems, and quality of life after 20 and 35 weeks, and 20 and 36 months.

Secondary therapist-related hypotheses are: In MAFT-D compared with TAU, stronger increase in observer-rated interpersonal skills after 35 weeks, and therapist-rated therapeutic skills, trait-like relational manner in therapy, emotional suppression, alexithymic traits (difficulties identifying and describing feelings) and satisfaction with supervision after 20 and 35 weeks, and 20 and 36 months.

The hypotheses regarding mediators of MAFT-D effectiveness are: MAFT-D generates more favourable outcomes via an improved therapeutic alliance and increased therapist skills to deal with alliance ruptures. Corresponding mediator variables are: (1) therapeutic alliance,^52^ (2) ratio of unresolved/resolved alliance ruptures,^22^ (3) convergence of patients’ and therapists’ alliance ratings over time,^14 53 54^ (4) interventions referring to the therapeutic relationship in the here and now,^13^ (5) nondirective supportive therapist’s techniques,^55 56^ (6) therapists’ competence in session (empathy) and^57^ (7) adherence to MAFT-D.^13 22^

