#### Variables to assess potential mediators for M-AFT-D effectiveness

Average level of therapeutic alliance across sessions (German short revised version of the Working Alliance Inventory, WAI-SR,^99^,^101^ assessed after each session, 12 items). Cronbach’s α for the total score: >0.90. Convergent validity is established.^100^Convergence of patient’s and therapist’s alliance ratings over time (patient and therapist versions of the WAI-SR, total scores of session ratings; see above).Ratio of unresolved/resolved alliance ruptures (Post-Session-Questionnaire–modified version, PSQ-mod).^102 103^ The first item asks whether a ‘problem or tension’ occurred in the relationship between patient and therapist during the session. If answered with ‘yes’, the intensity of the rupture and the degree to which it could be solved is specified. Despite the simple nature of the items, there are clear indications of their validity.^102 103^Therapists’ usage of interventions referring to the therapeutic relationship in the here and now as well as usage of nondirective supportive techniques (mean of the categories ‘repeating, paraphrasing, summarising’, ‘expression of emotional sympathy’, ‘validation’); Psychodynamic Intervention List, PIL, observer-ratings based on transcribed therapy sessions on the level of verbal statements,^104^ 0 ‘category characteristics do not apply at all’ to 5 ‘category characteristics completely apply’. Satisfactory reliability and convergent validity; inter-rater reliabilities ICC ‘expression of emotional sympathy’ 0.69, ICC ‘validation’: 0.68, ICC ‘repeating, paraphrasing, summarising’: 0.80, ICC ‘referring to the therapeutic relationship’: 0.78, ICC topic ‘therapist’: 0.87.^56 104^Therapists’ empathy (Empathy Scale^105^), total score, 10-items, observer-ratings of video-taped sessions, 0 ’no agreement at all’ to 3 ‘very strong agreement’. Cronbach’s α: 0.86.^106^Therapists’ basic communication skills (Clinical Communication Skills Scale–short version;^107^ total score, 14 items, observer-ratings of video-taped sessions, 4-point scale ‘not at all appropriately’ to ‘entirely appropriately’). Reliability and validity were demonstrated.^107^Therapists’ adherence to AFT, CBT, PDT (BIFS^58^), observer-ratings of video-taped sessions, 12 items each (three subscales). Good psychometric properties, criterion validity and adequate inter-rater agreement have been demonstrated repeatedly.^108^

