### Statistical analyses

Results are reported according to the Consolidated Standards of Reporting Trials (CONSORT) statement.^124^ Analyses are carried out with standard software: SPSS, V.29 or newer (IBM), SAS, V.9.4 or newer (SAS Institute), or R (V.4.3.3). A statistical analysis plan that contains the details of all planned analyses will be finalised before database lock.

Descriptive data are presented overall and separated by randomised group. As descriptive statistics, mean, SD, median, first and third quartile or minimum and maximum are calculated for continuous variables. For categorical variables, absolute and relative frequencies are reported.

First primary outcome (hypothesis I): We use a linear mixed model with repeated measures with changes from baseline as dependent variable, IG, therapeutic approach (CBT vs PDT), time and comorbid SCID5 personality disorder (yes vs no) as fixed effects, baseline BDI-II score as covariate, time by IG interaction, and cooperation centre, supervision group (if possible), therapist (=cluster) and patient as nested random effects. The interaction term is eliminated from the model if the corresponding interaction p value is >0.15. Measurement points up to and including the first follow-up (within the current funding period) will be considered. The contrast of the IG after 20 weeks is the result of the primary analysis. This result is considered in a confirmatory manner according to the approach described below. If the model fails to converge due to the complex cluster structure and variance components are estimated as zero, we will simplify the model stepwise by removing random effects.

Second primary outcome (hypothesis II): We perform a mixed logistic regression with the binary variable patient dropout after 20 weeks (yes vs no) as dependent variable, IG, therapeutic approach (CBT vs PDT) and comorbid SCID-5 personality disorder (yes vs no) as fixed effects, and cooperation centre, supervision group (if possible), and therapist as nested random effects.

The two primary hypotheses are hierarchically ordered and tested one after the other at the two-sided 5% level. Hypothesis II is only tested if hypothesis I could be rejected. If hypothesis I cannot be rejected, hypothesis II is no longer examined confirmatory but exploratory. This procedure ensures a family-wise type I error of 5%.

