Mediators: In path models, we test the hypotheses that the patient’s outcome is mediated by the average level of therapeutic alliance across sessions (WAI patient-rated); ratio of unresolved/resolved alliance ruptures (PSQ-Mod patient-rated; categorised in case of low variance); convergence of the patient’s and therapist’s alliance ratings over time (WAI patient-rated/therapist-rated); therapists’ usage of interventions referring to the therapeutic relationship in the here and now; therapists’ usage of nondirective supportive techniques (validation, expressing emotional sympathy, repeating, paraphrasing, summarising; PIL); therapists’ competence in session (empathy); therapists’ adherence to AFT techniques (BIFS-Subscale AFT). We will test for the presence of collider bias in these mediators (eg, using directed acyclic graphs), and, if detected, apply appropriate statistical methods to address it.

Additional analyses: (a) To test whether MAFT-D is equally effective in CBT and PDT, we examine the interaction between IG and therapeutic approach. Prior to this analysis, we examine baseline differences in clinically and theoretically relevant variables (depression severity, chronicity, comorbidity) between therapeutic approaches (CBT/PDT). Variables for which we detect clinically relevant group differences will be added as covariates. Cooperation centre will be included as a random effect. (b) We examine the adherence measure BIFS (adherence with AFT-techniques, observer-rated) as an outcome, with the same approach as in primary analyses (extent of contamination bias). (c) Safety endpoints are determined using frequency tables and, if possible, (mixed) logistic or linear regressions to compare the event frequencies/groups. (d) Subsidiary research questions concern predictors, moderators, and/or mediators (patient-related, therapist-related, patient-therapist match-related and process-related variables) of (a) therapeutic macro and micro outcomes (eg, dropout, alliance), (b) the effectiveness of MAFT-D (eg, presence of a personality or therapeutic orientation as moderators of MAFT-D effectiveness), (c) observer-rated interpersonal therapeutic skills and skills development and (d) the successful resolution of alliance ruptures.

Interim analyses are not planned. For secondary outcomes and analyses, missing values are not imputed and no adjustment for multiple testing is conducted.

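### The rupture mediator, a ratio of unresolved to resolved ruptures, has no value for patients with no rupture or with none resolved, and the stated fallback does not cover this

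*Protocol article*

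**What the plan says.** The Protocol article gives this mediator in the same form in three places:

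- Hypotheses and research questions, second of seven listed mediators: "ratio of unresolved/resolved alliance ruptures".
- Variables to assess potential mediators: "Ratio of unresolved/resolved alliance ruptures", measured with the modified Post-Session-Questionnaire (PSQ-Mod).
- Statistical analyses, Mediators: "ratio of unresolved/resolved alliance ruptures (PSQ-Mod patient-rated; categorised in case of low variance".

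The PSQ-Mod is completed after every session (Table 1). Its first item asks whether a problem or tension occurred. Only if the answer is yes are further details asked: "the intensity of the rupture and the degree to which it could be solved is specified".

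The end of the Statistical analyses section adds: "For secondary outcomes and analyses, missing values are not imputed and no adjustment for multiple testing is conducted". No rule is given for a patient without a resolved rupture.

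**The concern.** Resolved ruptures are the denominator. A patient with no rupture gives 0/0, and a patient with u ruptures, none of them resolved, gives u/0. Neither has a value. Yet the Background links ruptures to outcome and their repair to better outcome and less dropout, so the two patients stand at opposite ends of what the mediator is meant to measure.

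The hypothesis is that "MAFT-D generates more favourable outcomes via an improved therapeutic alliance and increased therapist skills to deal with alliance ruptures". Of the seven mediators, this is the one that directly records whether ruptures were repaired. Whether a patient has a value depends on having at least one resolved rupture, and hence also on how many sessions were rated. If MAFT-D increases resolution and reduces early dropout, as the trial expects, values would be missing more often in the TAU arm and among patients who leave early. Missingness would then be related to both arm and outcome, and a path model restricted to patients with a value would rest on a selected subset.

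**Working it through.** The article states no figure for this mediator, so there is none to reproduce. What follows is an illustration on assumed rates.

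**Inputs from the article.** Ratings are made after every session. Twelve completed sessions by week 20 is the per-protocol threshold, and weekly sessions would give about 20, so 15 lies between. The planned analysed sample is 232 patients. Expected dropout by week 20 is 30% in TAU and 12.5% in MAFT-D (Sample size calculation).

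**Assumptions.** S sessions are rated; each has a reported rupture with probability r; each rupture is resolved with probability q; sessions are independent. The article gives neither r nor q.

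**Formulas.**
- No rupture: (1 − r)^S
- No resolved rupture, hence no ratio: (1 − rq)^S
- At least one rupture, none resolved: (1 − rq)^S − (1 − r)^S

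**Results with q = 0.5** (components may differ from the total by rounding):

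| S | r | no rupture | rupture, none resolved | no ratio |
|---|---|---|---|---|
| 15 | 0.10 | 0.90^15 = 0.206 | 0.257 | 0.95^15 = 0.463 |
| 15 | 0.30 | 0.70^15 = 0.005 | 0.083 | 0.85^15 = 0.087 |
| 5 | 0.10 | 0.90^5 = 0.590 | 0.183 | 0.95^5 = 0.774 |
| 5 | 0.30 | 0.70^5 = 0.168 | 0.276 | 0.85^5 = 0.444 |

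If all 232 patients had 15 rated sessions, this would be 0.463 × 232 ≈ 107 patients at r = 0.10 and 0.087 × 232 ≈ 20 at r = 0.30.

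**Dependence on the number of sessions** (r = 0.20, q = 0.5): 0.90^5 = 0.590, 0.90^12 = 0.282, 0.90^20 = 0.122.

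**Dependence on resolution** (r = 0.20, S = 12): q = 0.5 gives 0.90^12 = 0.282; q = 0.7 gives 0.86^12 = 0.164. If the arms differed in this way, 28% would lack a value in one arm and 16% in the other, before any difference in dropout.

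**Wider range** (S = 12 to 20, r = 0.05 to 0.30, q = 0.3 to 0.9): from 0.2% (S = 20, r = 0.30, q = 0.9) to 83% (S = 12, r = 0.05, q = 0.3).

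**Varying rupture rates between patients.** With r drawn from a beta distribution with mean 0.10 (parameters 0.4 and 3.6), S = 12 and q = 0.5, the undefined share rises from 54% to 67%. A common rate for all patients is therefore not a pessimistic assumption.

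**Comparison with a proportion.** Unresolved divided by all reported ruptures lacks a value only when no rupture occurs. For S = 12, r = 0.10, q = 0.5 the undefined share falls from 54% to 28%; for S = 20, r = 0.20, q = 0.5 it falls from 12% to 1%. The remainder is entirely no-rupture patients, who can be given their own level.

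**The case against.** The strongest objection is that scoring rules belong in the analysis plan: "A statistical analysis plan that contains the details of all planned analyses will be finalised before database lock". That plan is not shown, and it may set a zero-denominator rule along with the cut-off that turns the graded resolution item into resolved or unresolved. This stands for the cut-off. It stands only in part for the ratio, because the article does more than name a construct. It fixes the quotient three times and anticipates trouble with it, but the remedy it states is for a different trouble.

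A second objection is that sparse ruptures make zero denominators common and may also make variance low, so categorisation could be triggered and could hold separate levels for none and all unresolved. That is possible but not stated. The variance of the ratio can be judged only among patients who have one, so the trigger may stay silent while many have none.

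Third, the article plans to check these mediators for collider bias. That may reveal a selection problem, but it does not give an undefined quotient a value.

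A reader might infer that these patients are dropped from the mediation analysis, and that they are the very patients the mechanism concerns. The article supports neither. It states no exclusion; not imputing is not the same as excluding; the underlying session ratings are observed; and a path model can be fitted with an incomplete mediator. The undefined group also includes patients with no rupture: at r = 0.10 and q = 0.5 they are 21 of 46 percentage points at 15 sessions and 59 of 77 at 5 sessions.

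**Conclusion.** The point holds as a poorly chosen derived variable. The ratio has no value in two opposite situations, the only stated fallback is keyed to something else, and the no-imputation rule leaves loss or ad hoc handling as the likely outcomes. Loss is a risk, not a stated plan.

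The size cannot be fixed from the article. With independent sessions, ruptures in 10 to 30% of sessions and half resolved, about 9 to 46% of patients with 15 rated sessions would have no value; varying the assumptions moves this from under 1% to over 80%. The direction is firmer than the size: fewer rated sessions and less resolution both mean more undefined values.

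The consequence is limited. One of seven mediators in a secondary analysis without multiplicity adjustment is affected. Neither primary hypothesis is touched, so this is a worthwhile improvement and not a threat to the trial's main conclusions.

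**What to change.** Replace the ratio, in all three places and in the analysis plan, with two measures that can be derived for every patient with at least one rated session:

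1. the number of reported ruptures, with the number of rated sessions as offset;
2. the number of reported ruptures left unresolved, or their proportion among reported ruptures, with no rupture as its own level.

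The change needs no new data, because the PSQ-Mod is already collected after every session, and it can be made before database lock. The cost is rewording one derived variable, carrying two measures where there was one, and less direct comparability with earlier reports that use a ratio. The ratio can still be reported descriptively among patients who have one, with the number who do not shown by arm.

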### Ethics and dissemination

The study is being conducted in compliance with the protocol, Good Clinical Practice, the Declaration of Helsinki and the CONSORT statement.^125^ All study patients, therapists and supervisors need to provide written informed consent to the main study team prior to their inclusion (see onlinesupplemental materials 1^4^: Example of Patient Consent Form; Example of Therapist Consent Form a/b; Example of Supervisor Consent Form). Study participation is completely voluntary and can be cancelled at any time without negative consequences. Patients who terminate study participation can continue their treatment. The study was approved by the Ethics Committee of the Psychologische Hochschule Berlin (EK2024/11). Additionally, we obtained secondary votes in each federal state where one or more study centres are located. Any major modifications to the study protocol will be covered by amendments and communicated to the relevant parties (eg, Data Safety and Monitoring Board, DSMB, see below). All personal data collected as part of the study, following the consent of the study participant, are subject to confidentiality and the provisions of the General Data Protection Regulation. All questionnaire, interview and rating data are collected pseudonymously within the secuTrial eCRF and REDCap surveys. This means that the participant’s name and all direct identifiers are replaced with a pseudonym, making reidentification outside of the study no longer possible. Access to the code key list that enables the association between study data and personal information of the study participant is limited to study staff explicitly authorised by the PI. The code key list is stored securely and separately from all other study data (eg, questionnaire data). The individual code key will be permanently erased following the completion of data collection and after the obligatory archiving time frame.

There is subject insurance for study patients. They receive the insurance confirmation and insurance conditions together with the study information. Assessments might be experienced as time-consuming. We do not expect other risks or adverse events due to study participation in patients or therapists. Positive effects resulting from treatments in both groups can be expected. There is no placebo or waiting list group. Both evidence-based treatments will be conducted according to state-of-the-art CBT/PDT and will be supervised by certified experienced psychotherapists. Frequency and dose of supervision correspond to usual standards.

Results will be published in peer-reviewed scientific journals following the ICMJE guidelines and disseminated to the general public, patient organisations and media.

Public involvement: Implications and recommendations for psychotherapy studies and further psychotherapy training are to be derived from the project results. These proposals will be discussed with relevant stakeholders (eg, the clinical directors of the training institutes).

### Quality assurance and safety

During the trial, quality control and quality assurance will be ensured through central monitoring based on the risk assessment of the study according to ICH Good Clinical Practice. The CTO will perform coordination, implementation and conduction of monitoring at the main study centre following its applicable Standard Operating Procedures (SOPs). Monitoring will be performed according to SOPs and study-specific requirements in accordance with the patient recruitment. The monitoring strategy will be defined in a monitoring plan with special attention to critical data and processes. The verification will focus on the key study data, for example, signed informed consent, adherence to inclusion and exclusion criteria and participant safety or adverse events. All the other data are checked on the basis of a representative sample, for example, documentation on primary objectives. Unclear and incomplete data will trigger increasing in-depth monitoring of the respective data.

Data management creates a data validation plan, containing additional logic checks for plausibility and consistency not available within the eCRF. Query analysis will be performed in SAS on an up-to-date export from the CRF. Found inconsistencies, implausible or missing data will be flagged by a data management query within the CRF. Possibly false information can be corrected through directly changing values within the eCRF or must be flagged as accepted failures or false positives. Changes within the documented information will be tracked via the audit trail, which is a core function of the eCRF.

After the last participant had its last visit, all queries and all centres were closed, and the database will be locked. Electronic documentation includes all exported files (SPSS, SAS, CSV, EXCEL), SAS scripts, data protocol and the closed database.

An independent DSMB will be regularly provided with all safety aspects of the trial and will review the safety data. Members of the DSMB are: [name] [name], International Psychoanalytic University, Berlin, licensed psychotherapist; [name] [name], Department of Psychosomatic Medicine and Psychotherapy, University Medical Center Mainz, experienced researcher and DSMB member in former psychotherapy trials and [name], Charité – Universitätsmedizin Berlin, independent statistician. At annual intervals, a meeting of the board will be scheduled to review whether the recruitment plan is on target, to ensure compliance with ethical principles, adherence to protocol, to check data quality and accuracy, and to advise whether to continue, modify or stop the trial. The DSMB will serve as a link to the funding organisation and provide them with information and advice. In the event of respective advice from the DSMB, the steering committee will finally decide whether to stop the trial (members: Professor [name], PI; Professor [name], statistician, Professor [name]—Institute for Medical Biostatistics, Epidemiology and Informatics, University Medical Center of the Johannes Gutenberg University Mainz, independent member and Professor [name]—Clinical Child and Adolescent Psychology and Psychotherapy, Bremen University, independent member).

Important events (eg, therapy dropouts, hospitalisation) can be reported by the therapist at any time. The study team will be alerted about incoming reports via email. Supervisors will be available at all study centres to decide about crisis interventions (eg, need for referrals). We will assess side effects/risks with questionnaires and interviews.
